### Participants and Eligibility

Study participants will be students or graduates, over the age of 18 years, of an Australian allied health or nursing training program and will have undertaken an NT placement as a student. Their placement, including any assessment of competence, will be concluded by the time of participation. Individuals who were already employed as a nursing or allied health professional and undertaking a placement as part of a postgraduate qualification will be excluded.

Framed by our pragmatist approach and as part of our due diligence around appropriate research designs, we considered using Australian Health Practitioner Regulation Agency (AHPRA) registration data rather than participant survey data. However, only about half of the professions of interest are registered through the AHPRA: Aboriginal and Torres Strait Islander Health Practitioner, Chinese medicine, chiropractic, dentistry, medical radiation, nursing and midwifery, occupational therapy, optometry, osteopathy, pharmacy, physiotherapy, podiatry, and psychology. Disciplines that are not registered include audiology, dietetics and nutrition, disability, exercise physiology, medical laboratory science, orthotics and prosthetics, paramedicine, social work, and speech pathology. Therefore, relying on AHPRA data to answer our primary question will not provide coverage of all the professions of interest.

The research design relies on access to the contact details of health professional students known to have undertaken work-integrated learning placements in the NT from 2017 onward. Flinders NT holds a secure database with the contact details of the placement students. These details were obtained for the purpose of supporting the placement; however, students consent to the use of their information for educational research purposes, such as our standard quality-improvement Student Satisfaction Survey regarding placement. Access to the database will allow the researchers to recruit participants to the study by contacting current and former students and inviting them to participate in the research.

### Ethics and Trial Registration

Ethics approval was provided by the Flinders University Social and Behavioural Research Ethics Committee (project No. 8245, expiring December 31, 2029). This study was registered with the Australian New Zealand Clinical Trials Registry (ANZCTR) (ACTRN12620000797976).

### Sample Size

In 2017, Flinders NT supported 462 students on placement from more than 20 universities across Australia. The average response rate to the standard quality assurance Student Satisfaction Survey regarding placement is about 30%. Based on 450 students per year undertaking placements and a conservative 15% response rate in the first year from students in the first three cohorts, approximately 203 participants will be added in the first year. Each year, another 450 students will be added to the sampling pool; however, over a 10-year period, we assume that the response rate will decline logarithmically by 1% each year, so that in the tenth year the response rate will be 6%. This equates to a total possible pool of 5400 participants who will each be offered up to 10 surveys, depending on the year they commenced in the study; however, with the declining response rates, we anticipate a final sample of 3175.

### Participant Recruitment

The recruitment process comprises an email invitation to participate. If a message bounces back from an email address, we will contact the participant seeking an email address via the last known telephone number in the database.

The research is comprised of annual online surveys, or phone surveys at the participant’s request. Survey 1 (ie, the Student Satisfaction Survey) is the first survey and is an evaluation of the student placement. The following year, Survey 2 (ie, the Work Location Survey) is sent, which comprises a 10-minute online survey asking about current work location and work location history and includes several questions regarding the influences on work location decisions. All subsequent years will use Survey 2 (ie, the Work Location Survey) to ask about work location and work location history, but this survey will not repeat the initial questions regarding demography and the NT placement.

Participation is voluntary and former students can also opt out of receiving any further surveys. In order to maximize the response rate while avoiding harassment of potential participants, we will send an email invitation to complete the survey, followed by two reminders that also contain the survey link. The reminders will include an option to cease receiving communications from Flinders NT.

We will also advertise the research on our social media sites (ie, Facebook, blog page, and website) in order to maximize exposure of potential participants to the study. This advertising will not contain a link to the survey but will simply describe the study and invite potential former placement students to contact us if they have not received an email invitation to participate.

To summarize, participants will be recruited in one of two ways, depending on their year of NT student placement:

Cohorts 1 and 2, which include health professional students known to have undertaken a Flinders NT–supported work-integrated placement during 2017 or 2018, will be contacted via their last recorded email address or phone number and invited to participate.Cohorts 3 to 12, which include health professional students undertaking Flinders NT–supported work-integrated placements from January 2019 and onward, will be emailed an invitation to participate at the conclusion of their placement.

Participants who complete Survey 1 will have their names placed in a random draw to win one of four vouchers valued at Aus $50 (US $38). Participants who complete Survey 2 will have their names placed in a random draw to win one of 10 vouchers valued at Aus $100 (US $76).

### Student Training and Placement

In this study, the intervention is having undertaken a student placement in the NT of at least one week in length. As part of standard accreditation processes, university-level health professional courses are required to demonstrate graduate competence in the application of knowledge and skills to patients and consumers of health care. Workplace-based placements, sometimes known as work-integrated learning activities, are a cornerstone of the curriculum because the students are working in health care workplaces under the supervision of a qualified health professional, learning to deliver the graduate competencies of the profession [43,44].

The supervision requirements, length, curriculum, and assessment of student placements vary according to the needs of the specific profession [12]. Whether the university pays the workplace or the workplace supervisor for providing the placement also varies. We recognize that the intervention includes student placement experiences that are not homogenous. From the perspective of workplaces, it is commonly assumed that student placements are a mutually beneficial recruitment strategy, allowing both the workplace and the student to consider the suitability and attractiveness of employment once they graduate [23,24,27,42,45].

### Retention Strategies

To maximize participation in the study, we will use a set of effective cohort retention strategies tested in previous cohort studies (eg, the Communicating Healthy Beginnings Advice by Telephone [CHAT] trial [46]). For example, we will send a thank-you e-card and birthday card to all participants. The relationship of the student with the placement coordinator or workplace supervisor may also influence survey participation, and we will seek ways to incorporate individual anecdotes into communications with students.

### Outcomes

The primary outcome of the study is the workplace location, assessed using the Modified Monash Model (MMM) [47], with MMM 4 and 5 considered rural and MMM 6 and 7 considered remote. The MMM defines whether a location is urban, rural, remote, or very remote, based on the Australian Statistical Geography Standard—Remoteness Areas (ASGS-RA) framework. The model measures remoteness and population size on an MMM category scale, ranging from MMM 1 to MMM 7. MMM 1 is a major city and MMM 7 is very remote. Any health service provision in areas classified as MMM 4 to 7, whether full time or part time, in the previous 12 months will be considered a rural or remote workplace location.

Baseline data (ie, Survey 1: Student Satisfaction Survey) will be collected following student placements and will include age, gender, degree program in which student is enrolled, length of placement, placement location, Indigenous status, NT residency, and rural origin.

### Data Analysis

To clarify the representativeness of the sample participants who respond each year, we will compare the distribution of the responders with the nonresponders in terms of age, gender, profession, length of placement, and Indigenous status. Descriptive analysis of deidentified aggregated data is planned. This will include survey response rates; number of student placements by profession and location, using the MMM and not town location; length and number of placements; gender; rural origin; NT residency; and influences on placement. Changes in work location will be analyzed by location. Factors associated with remote work location (ie, MMM 4 to 7 versus MMM 1 to 3) will be analyzed using logistic regression.

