Possible limitations of this study revolve around potential low participation rates, which could bias outcomes. Prompts, reminders, and acknowledgements (eg, birthday cards) will assist, but it may be that those most interested in rural and remote work will respond and that those who either had a negative experience of remote work while on placement or in some other context will choose not to participate. General information provided to the wider pool of nursing and allied health professional students about the study and the importance and benefits of rural and remote work will encourage participation in the study and will, more generally, promote interest in placements in the NT.

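### With planned response of 15% falling to 6%, the responder check omits collected variables closest to the selection the protocol itself expects, so an overstated rural proportion could go unnoticed

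*Protocol article*

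**What the plan says.** Three parts of the protocol article bear on this.

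- **Expected response (Sample Size).** The projection starts from "a conservative 15% response rate in the first year from students in the first three cohorts" and then assumes "the response rate will decline logarithmically by 1% each year, so that in the tenth year the response rate will be 6" per cent.
- **The representativeness check (Data Analysis).** The plan for every wave reads: "we will compare the distribution of the responders with the nonresponders in terms of age, gender, profession, length of placement, and Indigenous status". Rural origin and NT residency appear later in the same section, but only among the items for descriptive reporting. The Outcomes section lists the Survey 1 baseline data; besides the items used in the check, these include "placement location, Indigenous status, NT residency, and rural origin" (of which only Indigenous status is in the check). Survey 1 itself is the student's evaluation of the placement (Theoretical Framework and Study Design).
- **The expected selection and the response to it (Discussion, limitations paragraph).** The authors write that "it may be that those most interested in rural and remote work will respond", and that people with a bad experience of remote work, on placement or elsewhere, may stay away. Besides prompts, reminders and cards, they rely on information for the wider student pool about the study and "the importance and benefits of rural and remote work will encourage participation in the study".

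**The concern.** The check does not look where the protocol says the problem lies. None of the five listed characteristics directly measures interest in rural work or the quality of the placement. Rural origin, NT residency and placement location are plausible markers of the first, and the Survey 1 evaluation is a direct measure of the second. From the second Work Location Survey onward, a person's last reported MMM category is also on file, and it is closer to the outcome than anything else held.

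The primary outcome is work location, with any work in MMM 4 to 7 in the past year counted as rural or remote. The Discussion calls the proportion who go on to work remotely important for workforce planning, and the Context section ties the study to evaluating the funded program. If those working rurally answer more readily, that proportion is too high, and balance on the five listed characteristics would give false reassurance.

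A participation message built on the merits of rural work plausibly appeals most to the people already expected to over-respond.

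**Working it through.** **1. The planned response rates reproduce the article's own figures.** Inputs from Sample Size: 450 students a year, three cohorts in the first year, 15% response falling by 1 point a year over nine steps to 6%.

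- First year: 3 × 450 × 0.15 = 202.5, stated as 203.
- Pool: 12 × 450 = 5400, as stated.
- Final sample: summing 450 × (3 + i) × (0.15 − 0.01i) over i = 0 to 9 gives 3172.5. Rounding each year up gives 203 + 252 + 293 + 324 + 347 + 360 + 365 + 360 + 347 + 324 = 3175, as stated.

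So 3175 is a sum of yearly survey responses. Each annual proportion rests on 203 to 365 responses, and 85% to 94% of the pool is missing each year.

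**2. Size of the bias if response depends on work location.** Let p be the true proportion in MMM 4-7 and R the ratio of rural to non-rural response rates. Then

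observed = pR / (pR + 1 − p).

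The article gives no value for R, so 1.5 to 3 is an assumed range. The 30% is also an assumption. The Discussion cites a half and 23.7% from another study, and they are used here only as illustrative true values.

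| True p | R = 1 | R = 1.5 | R = 2 | R = 3 |
|---|---|---|---|---|
| 23.7% | 23.7% | 32% | 38% | 48% |
| 30% | 30% | 39% | 46% | 56% |
| 50% | 50% | 60% | 67% | 75% |

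For example, p = 0.30 and R = 2 gives 0.60 / (0.60 + 0.70) = 0.46. For 30% and 50% the bias is about 9 to 26 points.

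Such ratios fit within the planned overall rates. With p = 0.50 and 15% overall, R = 3 needs 22.5% against 7.5%. With 6% overall it needs 9% against 3%.

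**3. Comparison with sampling error.** The 95% half-width at 50% is 1.96 × √(0.25 / n): 6.9 points at n = 203 and 5.4 points at n = 324. The assumed bias exceeds this throughout, so intervals would look reasonably tight around a wrong value.

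**4. Trend.** The formula does not contain the overall response rate. If R stays constant while response falls from 15% to 6%, a flat true proportion still looks flat. A real change is rescaled by R / (1 + p(R − 1))². At R = 2 this is 2 / 1.69 = 1.18 for p = 0.30 and 2 / 2.25 = 0.89 for p = 0.50, so it may be stretched or compressed. A spurious rise needs R to grow: with a true 50% throughout, R moving from 1.5 to 3 would show 60% becoming 75%.

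**5. What the omitted variables could and could not repair.** Suppose (all assumed) 30% have rural origin, 60% of them and 30% of the others work rurally, and response depends on rural origin alone. The true proportion is 0.3 × 0.6 + 0.7 × 0.3 = 39%. If those of rural origin respond twice as often, their share of responders is 0.6 / 1.3 = 46%, and the observed proportion is 0.46 × 0.6 + 0.54 × 0.3 = 44%. At ratios of 1.5 and 3 it is 42% and 47%. Weighting on rural origin would restore 39%, but the five-item check need not show any imbalance. Selection on current work location beyond what such markers explain, as in step 2, is not removed by this weighting.

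**The case against.** **Availability.** Rural origin, NT residency, placement location and the evaluation come from Survey 1, which has about 30% response. Last reported MMM exists only for people who answered an earlier Work Location Survey. A comparison or weight built on them would therefore cover those groups, not the whole pool, unless the placement database holds the fields. This stands and limits what the fix can promise. But the Outcomes section takes the five listed characteristics (profession through the degree program) from the same Survey 1 baseline, so the article does not show that the omitted ones are harder to obtain.

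**Silence on correction.** A reader might infer that the primary proportion will be reported without any correction. The article does not say so. It is a condensed account, and weighting or sensitivity analyses may be set out in an analysis plan not shown here. What counts is the list that the article does fix.

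**The participation message.** A reader might infer that recruitment messages promote rural work and will worsen the bias. No invitation text is shown, and Participant Recruitment says the social media advertising is confined to describing the study. The Discussion speaks of general information to the wider student pool, which might also reach less interested students. Yet it does count on that information to raise participation, so the text supports that it could add to the selection, and no more.

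**The trend.** A reader might infer that falling response alone biases the ten-year trend upward. Step 4 of the working shows that it does not when the response ratio is constant.

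**Disclosure.** The authors openly state the bias and its direction, and they plan annual response rates and an annual responder comparison. That is to their credit, but it does not make the check sensitive to the bias that they describe.

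**Conclusion.** The concern holds in a bounded form. The article fixes a responder comparison that leaves out the collected variables nearest to the two response drivers it names. At 6% to 15% response, the check can pass while the level of the primary proportion is materially too high. The size, 9 to 26 points for true values of 30% and 50%, rests wholly on an assumed response ratio of 1.5 to 3. It shows what is possible, not what is expected. The claim concerns the level; a spurious upward trend needs the further assumption that the ratio grows. The effect of promoting rural work is a reasoned caution about direction that the documents do not quantify.

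**What to change.** 1. Extend the annual responder/nonresponder comparison to rural origin, NT residency, MMM category of the placement, Survey 1 evaluation and last reported MMM category, where held. State for each variable the group in which it is known: the full pool if the placement database holds it, otherwise Survey 1 completers or earlier Work Location Survey responders.
2. Report the annual proportion unweighted and, as a sensitivity analysis, weighted for response with the variables available for the group concerned.
3. Because weighting cannot remove selection on current work location itself, also report the proportion under rural to non-rural response ratios of 1, 1.5, 2 and 3. For an observed proportion q the implied true value is q / (q + R(1 − q)). An observed 50% would be shown as 50%, 40%, 33% and 25%. This needs no further data.
4. Keep study publicity and invitations neutral about work location, and remove promotion of rural work as a means of raising participation.

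The cost is modest analysis work, some added variance in the weighted estimate, and attention to the wording of publicity. No new data collection is needed for the variables already held.

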## Results

This study will generate unique data on the remote and rural work locations of nursing and allied health professional students who will have had placements in the NT of Australia. It will be able to determine what are the most important characteristics of those who take up remote and rural employment, even if outside the NT, and identify barriers to remote employment.

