## Discussion

The question of how many allied health and nursing students, as well as their characteristics, who have had a remote student placement go on to work remotely is a gap in the literature on remote work locations, which more typically focuses on medical students and to a lesser extent on nursing students. Filling this gap is important, given the federal funding invested in the RHMT Expansion Program as a strategy to grow a local remote health workforce. Given the national policy priority to recruit and retain health professionals in remote and rural areas, new insights into strategies to achieve this are needed. It is recognized internationally that building a remote and rural health workforce is a common challenge [48].

The analyses will be able to determine what are the most important characteristics of those who take up remote and rural employment, even if outside the NT, while adjusting for potential confounders, and will identify independent barriers to remote employment. A meta-synthesis of recruitment and retention of occupational therapists and physiotherapists in rural areas found that the availability of, and access to, practice supports; opportunities for professional growth; and an understanding of the context of rural practice were important [20]. Further, the calculation of the proportion of students who have had a placement in a remote setting and went on to work remotely is important for workforce planning. One study reported that 1 year after graduation, half of the allied health students who had had a rural placement were working in a rural or remote location, compared to 23.7% of all graduates from these disciplines [49]. It remains to be determined what proportion of students undertaking a remote placement will be working in a remote location in the short, medium, or long term after graduation.

The very low population density in the NT makes it a unique context to study remote health workforce issues. How the factors influencing the selection of remote health workplace locations compared to rural settings needs further study.

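### The only stated regression labels MMM 4 to 7 as remote, although the outcome definition reserves that word for MMM 6 and 7, so it cannot by itself support the promised remote-specific barriers

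*Protocol article*

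**What the plan says.** The Outcomes section of the protocol article sets the primary outcome on the seven-level Modified Monash Model, "with MMM 4 and 5 considered rural and MMM 6 and 7 considered remote". It then gives the combined group its own name: any health service work in MMM 4 to 7, full time or part time, "in the previous 12 months will be considered a rural or remote workplace location".

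The Data Analysis section states one regression, a logistic one, and words its subject as "Factors associated with remote work location (ie, MMM 4 to 7 versus MMM 1 to 3". No model for MMM 6 and 7 alone is described.

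The Results section promises two things in one sentence: the characteristics of people who take up remote and rural work, and to "identify barriers to remote employment". The Discussion repeats both, adds adjustment for confounders, and says that the analyses "will identify independent barriers to remote employment". It also presents the share of placement students who later work remotely as important for workforce planning, and it notes that how the factors behind remote choices compare with those behind rural ones is still to be studied.

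**The concern.** MMM 4 and 5 are rural, and not remote, in the outcome definition, yet they fall inside remote in the next section. Because the regression sentence explains its term with an explicit ie, it reads as a definition and not as loose usage. Nothing elsewhere in the article reconciles the two.

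The word matters because the article promises findings about remote employment, and this is the only stated model that could supply them. Under the any-work rule, a person who did some part-time work in an MMM 4 town during the year is a case in this model. If the output is reported under the label given, factors associated with rural or remote work will be published as factors associated with remote work. The article itself treats these as two settings whose determinants may need to be compared.

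**Working it through.** No figure in the article is in dispute, so there is none to reproduce. The check has two parts.

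**1. The definitions side by side**

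| Section | Term used | MMM range |
|---|---|---|
| Outcomes | rural | 4-5 |
| Outcomes | remote | 6-7 |
| Outcomes | rural or remote | 4-7 |
| Data Analysis (regression) | remote | 4-7, against 1-3 |
| Results, Discussion (barriers) | remote | no range given |
| Discussion (proportion working remotely) | remote | no range given |

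The second and fourth rows conflict. The third and fourth rows agree on the range and differ only in the name.

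**2. What the pooled model estimates**

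Take a binary factor, and MMM 1-3 as the reference. In people without the factor, let *a* be the odds of MMM 6-7 against MMM 1-3 and *b* the odds of MMM 4-5 against MMM 1-3. In people with the factor, these odds become *a* × OR_remote and *b* × OR_rural. The odds of MMM 4-7 against MMM 1-3 are the sum of the two parts, so

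OR_pooled = (*a* × OR_remote + *b* × OR_rural) / (*a* + *b*) = *s* × OR_remote + (1 − *s*) × OR_rural,

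where *s* = *a* / (*a* + *b*) is the MMM 6-7 share of MMM 4-7 jobs among people without the factor. The identity is exact for an unadjusted odds ratio. With covariates it holds within each covariate pattern.

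The article gives neither *s* nor any odds ratio. All values below are therefore assumptions, with *s* varied from 0.25 to 0.75.

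| OR_remote | OR_rural | *s* = 0.25 | *s* = 0.50 | *s* = 0.75 |
|---|---|---|---|---|
| 2.0 | 1.0 | 1.25 | 1.50 | 1.75 |
| 2.0 | 0.5 | 0.88 | 1.25 | 1.62 |
| 2.0 | 2.0 | 2.00 | 2.00 | 2.00 |

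For example, the first cell is 0.25 × 2.0 + 0.75 × 1.0 = 1.25. In the second row, 0.25 × 2.0 + 0.75 × 0.5 = 0.875, which lies on the other side of 1 from the remote odds ratio. In the third row the factor acts equally on rural and remote work, and pooling changes nothing.

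The pooled odds ratio therefore equals the remote one only when the rural and remote odds ratios agree. The pooled model cannot show whether they do.

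**The case against.** The strongest reply is that this is a missing word and not a wrong model. MMM 4-7 against 1-3 is exactly the category that the Outcomes section defines, and restoring the word rural to the regression sentence would remove the contradiction. The objectives concern work locations and the decisions behind them, without restriction to remote places. The Results and Discussion also promise findings on remote and rural work taken together, which this model delivers. A condensed article may leave further models to a fuller plan. The distortion is conditional as well: no document says that any factor acts differently on rural and remote work.

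Most of this stands. The model is valid for the combined aim, the dilution is a possibility and not a certainty, and the absence of a second model would be no finding on its own. What does not fall away is the stated conflict. The article gives remote two meanings in adjacent sections and then promises barriers to remote employment, with only the pooled model named to supply them. A fuller plan would inherit both meanings. Relabelling alone cures the regression sentence, but it leaves the remote-specific claim without a matching analysis unless that claim is also reworded.

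A reader might also infer that the headline proportion working remotely will be inflated by rural jobs. The documents do not support this. The Discussion refers to "the proportion of students who have had a placement in a remote setting and went on to work remotely" without any MMM range, the ie in Data Analysis governs only the regression outcome, and the seven-level scale allows MMM 6-7 to be reported separately.

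**Conclusion.** The point holds in a limited form and should be fixed. The regression outcome is mislabelled by the protocol's own definition, and the pooled model cannot by itself support independent barriers to remote employment as that definition understands remote. On the assumptions of a remote odds ratio of 2.0, a rural one of 1.0 and a remote share of 25% to 75%, the reported odds ratio would be 1.25 to 1.75. With opposite effects and a small remote share it could cross 1. With equal effects there is no distortion. The documents do not say which case applies.

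It would go too far to conclude that the study leaves the remote question unanswered. Where graduates work can be described by MMM category whatever the regression is called. The gap is confined to the remote-specific claims about factors and barriers.

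**What to change.** - Rename the stated model as rural or remote (MMM 4-7 versus 1-3). Keep it for the aim on remote and rural work together.
- For the remote claims, add either a three-level multinomial model (MMM 1-3, 4-5, 6-7) or a binary model of MMM 6-7 versus 1-5. The multinomial model gives the rural and remote odds ratios separately against the same reference, and so shows whether they differ. The binary model places rural workers in the comparison group.
- If neither model is wanted, restate the claims in the Results and Discussion as barriers to rural or remote employment.
- Use remote for MMM 6-7 throughout, including in reported proportions, and give MMM 4-5 and MMM 6-7 separately.
- Because any work in the previous 12 months counts, one person may have worked in both ranges. A three-level outcome needs a stated rule for placing that person.

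The cost is a change of wording and one further model on location data already to be collected. The MMM 6-7 estimates will rest on fewer cases and be less precise. Fixing the categories now also prevents the cut-point from being chosen after results are seen, in a study whose annual surveys run to 2029.
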